### Statistical analyses

CODEC provides an extremely rich longitudinal dataset which will be made available to the community through a managed access protocol. The CODEC dataset will generate a large number of potential questions, novel approaches and challenges. However, CODEC also sets out to answer a set of key preregistered hypotheses. Below we outline the general analytic framework, as well as 23 key preregistered predictions and analyses (https://osf.io/jzu6n/), all written prior to the first data collection.

#### Quantitative framework

To quantify variability, a wide range of measures are available. However, some simple summary metrics such as iSD (individual standard deviations) or ICV (coefficient of variation) do not take autoregressive structures or global change into account [119] and tend to ignore measurement error inherent in variability [120]. To overcome this challenge, we use a relatively new, flexible, integrative mathematical framework of Dynamic Structural Equation Modelling (DSEM) [121–123], allowing us to simultaneously estimate all components of the sequence of task trials. Moreover, each of the four key parameters (mean, trend, inertia and residual variability) can be estimated as a random effect (i.e., allowing for variations between individuals) within a multilevel Structural Equation Modelling (SEM) framework. Fitting a DSEM to the planned ‘burst’ measurement therefore results in a rich set of variability estimates across individuals, tasks and temporal resolutions.

#### Key hypotheses

**Aim (1) reliably measure individual differences in cognitive variability across timescales and tasks:** to overcome previous challenges in reliably measuring variability, we first use DSEM to estimate individual differences in variability across task domains (between the various tasks we assess), and across levels of temporal resolution (from trial-to-trial, across sessions within days, from day-to-day and from year-to-year). In these DSEM models we simultaneously estimate the mean, trend, autoregression, and residual standard deviation (see [25, 68], or [7] for more details). Moreover, each of these parameters is estimated as a random effect (i.e., as varying between individuals) and compared to a model with fixed effect parameters (i.e., assumed constant between individuals). One central expectation is that within person fluctuations are not (solely) measurement error, which we would expect to be similar across individuals. Instead, we hypothesise that within-person variability reliably differs between individuals for a given dataset with suitable temporal resolution. As such, our first hypothesis is that*Hypothesis 1.1: A DSEM with a parameter estimating the variance of subject-specific deviations in trial-to-trial variability will be preferred over a model that omits it, across all tasks.**Hypothesis 1.2. A DSEM with a random-effects structure that freely estimates variability in mean performance from day-to-day (or session-to-session) will be preferred, over a model that only estimates fluctuations at faster timescales.*

Second, we expect that individual differences in variability will be correlated across tasks, but more weakly so than individual differences in (average) performance. Moreover, we expect that these differences cannot be fully captured with a single latent factor [7]. As such, our second preregistered prediction is as follows*Hypothesis 1.3: After extracting individual-level estimates of variability, we will fit a single factor model of variability across the 5 tasks, separately for each timescale. This unidimensional model will not fit sufficiently well (as indexed by a significant chi-square and an RMSEA* > *0.05). This prediction will hold for each timescale (trials, sessions, days).*

**Aim (2) Underlying mechanisms:** in the imaging arm, we consequently use key predictors of interest in the deeply phenotyped subsample (*N* = 200) to test mechanistic hypotheses about the (hypothesised) causes of individual differences in variability. In terms of brain structure, we first test the known association between larger grey matter volume and better cognitive performance to replicate previous findings [124]. Then, we test the neural noise hypothesis, which suggests that better myelination of the brain is associated with less variability due to decreased signal loss [73].*Hypothesis 2.1: Children with larger grey matter volume will demonstrate better cognitive performance in the behavioural tasks.**Hypothesis 2.2: Children with larger white matter volume (better myelination) will demonstrate higher BOLD signal variability (potentially reflecting lower neural noise).**Hypothesis 2.3: Children with higher tract-based indirect measures of myelination (both in white matter tracts and in grey matter) between frontoparietal executive systems (specifically: the SLF, ATR, IFOF and Forceps Minor) will show less variability. This effect will manifest most strongly for complex tasks, as those are most dependent on multi-region information integration.**Hypothesis 2.4: Myelination increases during childhood. Children with steeper increase in myelination (both in white matter tracts and in grey matter) will show sharper decrease in behavioural variability between year 1 (*~*8 years old) and year 3 (*~*10 years old).*

Optimal cognitive performance often involves finding a balance between exploring different strategies and exploiting successful ones. For instance, for a matrix reasoning task, individuals may use either elimination (ruling out response options) or constructive matching (building a prediction, and then examining whether it is among the available options, [125]). Using fMRI data, we will study whether differences in strategy use govern individual differences in variability, and whether we can identify neural networks associated with different strategies as a potential mechanism underlying trial-to-trial variability. While exploring different strategies may temporarily reduce performance, it could facilitate long-term improvement by promoting exploration and adaptation. We also use eye-tracking data to infer foci of attention and task strategies, and changes in pupil dilation during the fMRI task blocks as a proxy for fluctuations in underlying noradrenergic and dopaminergic processes.*Hypothesis 2.5: Individuals with greater variability (estimated with DSEM) will show a larger number of response strategies within the fluid reasoning task (estimated through eye tracker analysis, cf. *[66]*).**Hypothesis 2.6: Greater fMRI resting state variability (as quantified by blood oxygenation level-dependent standard deviations) is associated with better, and less variable behavioural performance in children.**Hypothesis 2.7: Different trial strategies, estimated using eye tracker analysis *[66]* will be associated with recruitment of neural networks that differ qualitatively (i.e., different centroid and negligible spatial overlap).*

Additionally, we study the role of psychological (e.g., mind wandering, sleep, mood) and environmental (e.g., socio-economic status (SES)) factors on between- and within-person differences in variability by using them as predictors in a (regularised) SEM.*Hypothesis 2.8: Individuals from lower SES backgrounds will show greater day-to-day variability.**Hypothesis 2.9: Individuals with greater mind wandering tendency will show greater cognitive variability, especially at the trial-to-trial level.**Hypothesis 2.10: Days or testing sessions with greater negative affect, poorer sleep, and/or more background noise will be days or testing sessions with greater variability as well as poorer mean performance.**Hypothesis 2.11: Tasks ranked as less enjoyable (individually) will be tasks with greater variability as well as poorer mean performance (when adjusting for task difficulty).*

To understand variability within individuals, we have to consider not only unique within-subject predictors but also potential subgroup differences. Neubauer et al. [43], identified subgroups of different profiles within a population for whom mood had varying effects on variability (i.e., low mood leading to higher variability, high mood leading to higher variability, mood having little effect on variability, and a group where both low and high mood lead to higher variability). We will use mixture models to identify subgroups within the population, allowing for the coupling of variability with factors like mood, sleep, background noise, and motivation (task rank). Specific subgroups that will be identified due to interactions between these factors are mostly exploratory, as not enough research has investigated this question so far.*Hypothesis 2.12 (exploratory): The overall sample will consist of a mixture of distinguishable subgroups in the population with a subgroup having a negative impact of mood, sleep quality, background noise, and motivation (task ranking) on variability and a subgroup having no negative impact of mood, sleep, background noise, and motivation (task ranking) on variability.*

The parents or guardians of the subgroup taking part in the imaging study are also asked to perform the cognitive tasks on tablet at each session. These scores act as predicting variables in latent mixed models to explore possible hereditary correlations.*Hypothesis 2.13: Variability will be correlated between parents and children*

**Aim (3) Long-term consequences:** Our last class of predictions concerns long-term outcomes of individual differences in variability. Using latent growth curve models, we will study how variability and mean performance evolve over time, and how differences in variability are associated with faster, or slower, rates of cognitive development and the emergence of subclinical neurodevelopmental symptomatology (e.g. ADHD symptoms).*Hypothesis 3.1: Variability will decrease over developmental time. Specifically, a growth model with variability as observed scores will show a mean negative slope (less variability over time), as well as significant slope variance (individual differences in the rate of change over time). A basis model (which can capture a decelerating decrease) will outperform a linear model.**Hypothesis 3.2: Changes in variability across tasks will show distinct developmental trajectories, as variability reflects task-specific expertise. Specifically, a multivariable latent growth curve model with freely estimated slope covariances will fit better than a simpler model with these covariances fixed to unity (i.e., a unidimensional factors-of-curves model), in line with distinct developmental trajectories.**Hypothesis 3.3: Greater variability on simple tasks, and low temporal resolution (day-to-day), is associated with poorer long-term outcomes (shallower developmental slopes).**Hypothesis 3.4: Great variability on complex tasks, but only at the trial-to-trial level, is associated with better long-term outcomes (steeper slopes).**Hypothesis 3.5: Greater variability at baseline will be associated with stronger ADHD symptomatology at baseline, as well as more rapid increase in ADHD related symptomatology.*

A secondary long-term aim is to link individual differences in variability to longitudinal academic success (Cito-scores).*Hypothesis 3.6: Greater variability on simple tasks, and low temporal resolution (day-to-day), is associated with poorer long-term academic achievement (shallower developmental slopes).**Hypothesis 3.7: Great variability on complex tasks, but only at the trial-to-trial level, is associated with better long-term academic outcomes (steeper slopes).*

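### Hypothesis 1.2 tests whether day- or session-level fluctuation exists, not whether children differ in it, although it is introduced as following from the claim that they do

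*Protocol article*

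**What the plan says.** All references are to the protocol article, Statistical analyses.

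- **The aim.** Under Key hypotheses, Aim 1 is to "reliably measure individual differences in cognitive variability across timescales and tasks".
- **The claim.** The lead-in says that pure measurement error should look alike from child to child. Against that, "we hypothesise that within-person variability reliably differs between individuals for a given dataset with suitable temporal resolution". The first two hypotheses are then presented as the consequence of this claim.
- **H1.1, trial level.** "A DSEM with a parameter estimating the variance of subject-specific deviations in trial-to-trial variability will be preferred over a model that omits it".
- **H1.2, slower levels.** The prediction is that a DSEM whose random-effects structure "freely estimates variability in mean performance from day-to-day (or session-to-session) will be preferred, over a model that only estimates fluctuations at faster timescales".
- **A general comparison.** The same paragraph says that the mean, trend, autoregression and residual SD are each given random effects, and that this is set against a model holding them fixed across children.
- **Later use.** H1.3 takes child-level variability estimates at trial, session and day level. H2.8 states "Individuals from lower SES backgrounds will show greater day-to-day variability". H3.3 states "Greater variability on simple tasks, and low temporal resolution (day-to-day), is associated with poorer long-term outcomes", and H3.6 makes the parallel prediction for academic achievement.

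**The concern.** H1.1 and H1.2 follow from one claim but test different things. H1.1 adds a between-child variance of variability and compares it with a model lacking only that parameter, which is the claim itself at trial level. H1.2 adds the whole day or session level and compares it with a model that has no such level. Its null is that day means do not vary within a child beyond trial noise. It is not that all children vary equally from day to day.

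H1.2 can therefore succeed in the situation that the lead-in treats as no support: fluctuation of the same size in every child. Such fluctuation needs no difference between children in variability. Different item draws from one session to the next are one possible source, since each session uses a pseudorandom three of the five tasks and vocabulary items are sampled from a large pool.

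What is at stake is interpretation. At the slower timescales Aim 1 would lack a stated test of its own claim. A null result in H2.8, H3.3 or H3.6 could then mean either that day-level variability is unrelated to the outcome or that children hardly differ in it.

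**Working it through.** **Step 1: the nested models.** For one task, let the mean of child *i* on day *d* be the child's level plus a day deviation with variance τᵢ², plus trial noise with variance σ²/m for *m* trials.

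| Model | Day-level variance |
|---|---|
| A | none: τᵢ² = 0 for all children |
| B | common: τᵢ² = τ² for all children |
| C | child-specific: log τᵢ has its own mean and variance |

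H1.2's comparator is A. Its larger model is B or C, depending on how the random-effects wording is read. The claim that children differ is C versus B. Since A omits the day level, B versus A and C versus A are both satisfied by a common τ² > 0.

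**Step 2: inputs.** From the article: 600 children, 5 days per burst, about 200 children in the imaging arm. Assumed, because the article does not give them: 20 trials per child, day and task; τ/σ of 0, 0.1, 0.2, 0.3 or 0.5; BIC as the preference criterion. The article states no figure for H1.2, so there is none to reproduce.

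**Step 3: hand check of B versus A with identical τ, N = 600, τ/σ = 0.1.**
- Inflation of the day mean square: 1 + mτ²/σ² = 1 + 20 × 0.01 = 1.2.
- Degrees of freedom: 600 × 4 = 2,400 between days within child; 600 × 5 × 19 = 57,000 within day.
- Pooled variance under A: (2,400 × 1.2 + 57,000)/59,400 = 1.00808.
- Approximate likelihood ratio: 59,400 × ln 1.00808 − 2,400 × ln 1.2 = 478.1 − 437.6 = 40.5.
- BIC penalty for one parameter: ln(600 × 5 × 20) = ln 60,000 = 11.0.

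The likelihood ratio is well above the penalty although no child differs from another. The simulated mean was 41.0.

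**Step 4: simulation.** Gaussian trials, marginal maximum likelihood, 100 runs per row. The last column is a 5% boundary likelihood-ratio test (critical value 2.706).

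| N | τ/σ | Spread of log τᵢ (SD) | Mean LR, B vs A | B over A, BIC | C over A, BIC | C over B, BIC | C over B, 5% test |
|---|---|---|---|---|---|---|---|
| 600 | 0 | 0 | 0.4 | 0% | 0% | 0% | 0% |
| 600 | 0.1 | 0 | 41.0 | 100% | 96% | 0% | 4% |
| 600 | 0.2 | 0 | 487.1 | 100% | 100% | 0% | 3% |
| 600 | 0.3 | 0 | 1,694.8 | 100% | 100% | 0% | 2% |
| 600 | 0.5 | 0 | 6,655.9 | 100% | 100% | 0% | 4% |
| 200 | 0.3 | 0 | 577.6 | 100% | 100% | 0% | 5% |
| 600 | 0.3 | 0.4 | 2,727.8 | 100% | 100% | 100% | 100% |
| 600 | 0.5 | 0.4 | 9,586.4 | 100% | 100% | 100% | 100% |

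With no day-level variance, H1.2 is correctly not confirmed. With some, it is confirmed whether or not children differ (compare the two N = 600 rows at τ/σ = 0.3). Reading the larger model as C does not change this. Only C versus B separates the two situations.

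**The case against.** The strongest reply is that the comparison is already there. The general sentence refers to DSEMs described as covering several temporal resolutions, and residual SD is among the parameters to be compared as random versus fixed. If that includes a day-level residual SD, it is C versus B. This partly stands: the wording allows it. But the Quantitative framework section describes those parameters as components of the sequence of task trials, no day- or session-level variance is named, and the only stated criterion for slower timescales is H1.2. The preregistration and cited method papers, not shown here, may settle it.

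Second, H1.2 does not itself mention differences between children and tests what it literally predicts. That stands, and it limits the point to the mismatch with the claim from which H1.2 is derived.

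Third, the simulation builds in a non-zero day variance and then detects it. That is also fair: the high percentages are power for H1.2's own hypothesis. It used Gaussian trials without trend or autoregression, and child-specific day deviations of equal SD. It does not represent shifts shared by a whole classroom, a level the article says is modelled.

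A reader might infer that later hypotheses would be falsely confirmed. The documents do not support this. If children did not differ in day-level variability, H2.8, H3.3 and H3.6 would have no true child-level variation to relate to anything, and the expected result is null.

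**Conclusion.** The point holds as a mismatch between claim and test. As printed, H1.2 establishes that performance fluctuates at the day or session level. It does not establish that children differ in that fluctuation, which is the Aim 1 claim it follows from. The logic needs only some day-level variance. The percentages depend on the assumed 20 trials per day, the SD ratios and BIC.

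Two stronger conclusions are not supported. H1.2 is not an invalid test, because it fails when there is no slower fluctuation. Nor can it be said that the study never compares random with fixed day-level variability, because the general sentence is ambiguous and the fuller sources are not shown. The change is worth making because it is cheap and lets Aim 1 answer its own question at the slower timescales.

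**What to change.** State H1.2 as a three-model comparison for each task and slower timescale: (i) no day or session variance; (ii) a variance common to all children; (iii) a child-specific variance, random on the log scale. Let the statement that fluctuation exists at that timescale rest on ii versus i, and the statement that children differ at that timescale rest on iii versus ii.

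Report the iii-versus-ii result next to H1.3, H2.8, H3.3 and H3.6, so that a null there can be read in light of whether day-level variability differs between children. Those hypotheses should not be made conditional on it, since that would subject preregistered tests to a pretest. If the general random-versus-fixed comparison was already meant to cover day- and session-level variance, say so explicitly.

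The cost is one extra model per task and timescale and a change of wording. The downside is that Aim 1 may turn out not to be supported at some slower timescales.

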### Individual differences in cognitive variability and their specificity

Our first focus is on the extent to which individuals fluctuate in cognitive performance and how these fluctuations differ between individuals. This relatively simple question allows us to establish first and foremost the nature of systematic and replicable individual differences in cognitive fluctuations, and to what extent these fluctuations provide valuable information about individuals.

We investigate such individual differences in cognitive variability across different timescales (trials, sessions, days, seasons and years) and cognitive tasks (visuospatial working memory, reasoning, processing speed, vocabulary, and exploration). In line with previous studies, we suspect there is valuable information in fluctuations across different timescales, including day-to-day and day-of-week dynamics [23], and seasonal trends [24]. Crucially, recent evidence [16, 25, 26] suggests that individual differences at different temporal resolutions (e.g., trials versus days) are at most weakly correlated, suggesting distinct underlying mechanisms. Moreover, we also examine the degree of similarity across tasks – In other words, if children are relatively variable on one task, are they also likely to be more variable on others? Our previous findings suggest trial-to-trial variability is likely correlated across tasks, but much more weakly so than mean performance [7].

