### Sample size considerations

#### Behavioural arm

The number of subjects needed in DSEMs have previously been examined through a series of Monte Carlo simulations [126]. Focusing on univariate two-level autoregressive models, they demonstrate that the DSEM performs well across a range of scenarios. For example, the estimation stability gained from a larger number of subjects is greater than the benefits of a large number of trials. Crucially, they demonstrate that DSEM achieves a highly reliable estimate of individual differences in trial-to-trial cognitive variability with anywhere upwards of 15 trials, given 200 subjects (average estimate over 500 repetitions/true value = 0.88, [126]).

In terms of power to detect significant associations, the behavioural arm of the CODEC study is effectively at ceiling (see Fig. 9) for effect sizes we observe in previous literature, including the effect of mind wandering on variability (*r* = -0.53, 100% power; [52]), variability on ADHD symptoms (*r* = 0.39, 100%; [94]), and inattention on variability (*r* = 0.24, 100% power; [19]). For the full behavioural sample (*N* = 600), even small effect sizes (*r* = 0.11) can be detected with 80% power.

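### Hypothesis 1.3 rests only on misfit of a one-factor model, a rule that loses power as all cross-task correlations shrink and that full task-specificity cannot meet

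*Protocol article*

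**What the plan says.** Under Key hypotheses, Aim 1, the article states two expectations. The first is that "individual differences in variability will be correlated across tasks, but more weakly so than individual differences in (average) performance". The second is that "we expect that these differences cannot be fully captured with a single latent factor". The background section on individual differences and their specificity is firmer on the first: "trial-to-trial variability is likely correlated across tasks, but much more weakly so than mean performance". No numerical correlation is given in either place.

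Hypothesis 1.3 is derived from these expectations. Individual-level variability estimates are extracted, and then "we will fit a single factor model of variability across the 5 tasks, separately for each timescale". The decision rule is: "This unidimensional model will not fit sufficiently well (as indexed by a significant chi-square and an RMSEA" greater than 0.05. It is a conjunction over timescales: "This prediction will hold for each timescale (trials, sessions, days").

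The hypothesis sets no criterion on loadings, on variance explained, on the size of the cross-task correlations, or on a comparison with mean performance. It does not say how a well-fitting model with low loadings would be read.

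**The concern.** Chi-square and RMSEA measure how far the observed correlations depart from a one-factor pattern. They do not measure how strong the common factor is. If all correlations shrink together, the possible departure shrinks with them. In the limit of no correlation there is nothing left to misfit.

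Two quite different states therefore produce the same result, failure to meet the rule: one strong general factor, or no common factor at all. The second is the extreme form of what the authors expect.

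Error in the extracted scores pushes the same way, because it attenuates every cross-task correlation. The Quantitative framework section criticises simple variability metrics because they "tend to ignore measurement error inherent in variability". Using extracted estimates as if they were observed can bring part of that problem back at the second stage.

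At stake is the interpretation of the only listed test of how levels of variability are structured across tasks.

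**Working it through.** **Inputs from the article.** Five tasks; N = 600 (Sample size considerations, Behavioural arm); RMSEA limit 0.05; three timescales.

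**Assumptions.** Chi-square tested at 5%; normal data; scores from all 600 children. The cross-task correlations are assumed throughout and varied. The article gives no power or error rate for Hypothesis 1.3, so there is no stated figure to reproduce.

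**Step 1: the binding threshold.** Five indicators give 5 × 6 / 2 = 15 moments. The model has 10 parameters, so df = 5. With RMSEA = √[(χ² − df) / (df × (N − 1))], RMSEA > 0.05 requires χ² > 5 + 5 × 0.0025 × 599 = 12.49. The 5% critical value of chi-square on 5 df is 11.07, so the RMSEA limb decides.

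**Step 2: independent tasks.** A one-factor model with zero loadings fits exactly. The central chi-square on 5 df exceeds 12.49 with probability 2.9%. Two simulated runs of 400 data sets with uncorrelated tasks met the rule 0 times and once, so 2.9% is an upper figure.

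**Step 3: a true two-factor structure.** Assume two factors (2 + 3 tasks) with equal loadings λ and factor correlation φ. Correlations are λ² within and φλ² between clusters. The one-factor model is fitted by maximum likelihood to this matrix S, minimising F = ln|Σ| + tr(SΣ⁻¹) − ln|S| − 5. The non-centrality is 599 × F₀, and the probability of meeting the rule is that of a non-central chi-square (5 df) exceeding 12.49.

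For φ = 0.5:

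| λ | Within / between r | F₀ | 599 × F₀ | P(rule met), one timescale |
|---|---|---|---|---|
| 0.5 | 0.25 / 0.125 | 0.0351 | 21.0 | 94% |
| 0.4 | 0.16 / 0.08 | 0.0131 | 7.9 | 47% |
| 0.3 | 0.09 / 0.045 | 0.0039 | 2.3 | 12% |

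Simulation gave 43% at λ = 0.4, slightly below the approximation.

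**Step 4: vary the factor correlation.**

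| φ | λ = 0.5 | λ = 0.4 |
|---|---|---|
| 0.8 | 25% | 9% |
| 0.7 | 55% | 18% |
| 0.5 | 94% | 47% |
| 0.2 | 99.8% | 78% |

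With loadings fixed, more distinct factors make the rule easier to meet.

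**Step 5: a second pattern.** Two clusters with a fixed 3:1 ratio of within- to between-cluster correlation, 400 simulated data sets per row:

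| Within / between r | Population RMSEA | P(rule met) |
|---|---|---|
| 0.30 / 0.10 | 0.122 | 100% |
| 0.21 / 0.07 | 0.083 | 94.5% |
| 0.15 / 0.05 | 0.059 | 60% |
| 0.09 / 0.03 | 0.035 | 10.5% |

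The structure is two-dimensional in every row, and only the strength changes. When all correlations are equal, one factor is true at any strength: the rule is met 2.5% of the time at r = 0.6 and 3.5% at r = 0.1.

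**Step 6: score error.** An observed loading equals the true loading times the square root of reliability. A true loading of 0.8 with an assumed reliability of 0.25 becomes 0.8 × 0.5 = 0.4. At φ = 0.5 this takes the probability from 100% to 47%. On the design, a burst has 2–3 sessions a day for 5 days with three of five tasks per session. That is 10–15 sessions, or 6–9 per task, over at most 5 days.

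**Step 7: three timescales.** If the timescales were independent with equal power, 94%, 47% and 12% become 0.94³ = 83%, 0.47³ = 10% and 0.12³ = 0.2%. Positive dependence would give values between these and the single-timescale figures.

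**Step 8: the comparison with means.** The article announces 23 key predictions and lists 3 + 13 + 7 = 23. None compares cross-task correlations of variability with those of mean performance.

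**The case against.** Much of the opposing case is sound. Chi-square and RMSEA are standard indices for the second expectation, that one factor is not enough. The authors expect some correlation, not independence, so the limiting case lies outside their stated prediction. If the rule is not met, their own hypothesis goes unsupported, which is a conservative error. A fitted model also yields loadings, so near-zero loadings could be seen.

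Three stronger readings are tempting, and the documents do not support them:

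- **Weaker correlation always improves fit.** It does so only when all correlations shrink together. If only the between-cluster correlations weaken, misfit grows (Step 4).
- **The outcome reflects reliability and not dimensionality.** It reflects both. At loading 0.5 the probability runs from 25% to 99.8% on factor correlation alone.
- **The plan would read good fit as one general variability trait.** The article does not say so. It is silent on how good fit is read.

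A reader might also infer that session- and day-level scores are the noisiest. The few occasions per task make that plausible, but no reliability is given. The extraction method is not stated either, and the preregistration behind the article may hold more detail.

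What remains is that the rule is stated in full with its thresholds. Followed as written, it counts complete task-specificity against a hypothesis derived from an expectation of weak, not single-factor, structure.

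**Conclusion.** The concern holds in a limited form. Misfit of a one-factor model is a usable test of multidimensionality when correlations are moderate and clustered: under the patterns tried, about 94% or more per timescale with within-cluster correlations of at least 0.21 and between-cluster correlations of half that or less. It is unsuitable as the sole evidence for Hypothesis 1.3, because its power falls as all correlations shrink and it cannot register full task-specificity.

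The figure of at most about 3% under independence needs only N = 600, five tasks and the stated limit. The others rest on assumed loadings, factor correlations and cluster patterns. At loading 0.4 the range is 9% to 78%, so the practical risk cannot be fixed from the article. The three-timescale requirement lowers any of these figures further. Separately, the expectation of weaker correlation than for mean performance has no test among the listed predictions.

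**What to change.** Keep chi-square and RMSEA as the test of multidimensionality, but do not let good fit alone decide Hypothesis 1.3. Add, for each timescale:

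1. The mean cross-task correlation of variability minus that of mean performance. The expectation is supported if the 95% interval lies below 0.
2. The share of variance in the task variability estimates explained by the general factor (or its loadings), with an interval. State in advance that good fit with low loadings is read as task-specificity, not as one general trait.
3. Estimation error in the variability scores carried forward, through plausible values or through random-effect correlations from a joint DSEM where that is feasible.

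A test of correlations fixed at 1 should not replace the one-factor test. One factor allows task-specific variance, so correlations of 1 are a different and stricter null.

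The cost is a preregistration update and somewhat heavier analysis, with no new data.
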